#### Economic analysis

A cost-effectiveness and/or cost-utility analysis from a Health Service perspective (financer perspective) will be performed. The time horizon is 2 years and will include only direct health (medication and healthcare use of services including outpatient and emergencies visits and hospital admissions). The Quality-Adjusted Life Years (QALYs) will be calculated to estimate the benefit calculating the utility improvement measure by EuroQoL-5D-5 L.

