## Methods

### Aims

We refer to our TV-based Assistive Integrated Service intervention as TV-AssistDem. The main objective of this project is:
To evaluate the effectiveness of TV-AssistDem on quality of life among people with mild cognitive impairment or mild dementia after 12 months follow-up in comparison to controls. We hypothesize that the use of TV-AssistDem over 12 months can result in an improvement in quality of life when compared to a matched control group of patients not using TV-AssistDem.

The secondary objectives of this project are:
To evaluate the impact of TV-AssistDem on caregiver quality of life after 12 months of follow-up. We hypothesize that quality of life will be significantly improved in caregivers after the intervention when compared to matched controls over 12 months.To evaluate the impact of TV-AssistDem on caregiver burden after 12 months of follow-up. We hypothesize that burden will be significantly reduced in caregivers after the intervention when compared to matched controls over 12 months.To evaluate the impact of TV-AssistDem on patient treatment adherence after 12 months of follow-up. We hypothesize that treatment adherence will be significantly increased in patients in the intervention group when compared to matched controls over 12 months.To evaluate the impact of TV-AssistDem on patient treatment compliance after 12 months of follow-up. We hypothesize that treatment compliance will be significantly increased in patients in the intervention group when compared to matched controls over 12 months.To evaluate the impact of TV-AssistDem on functional status after 12 months of follow-up. We hypothesize that functional decline will be significantly reduced in patients in the intervention group when compared to matched controls over 12 months.To test the economic and financial impacts of using the TV-AssistDem after 12 months of follow-up. We hypothesize that after accounting for the estimated per patient costs of our intervention, patients in the intervention group will have significantly lower healthcare costs after 12 months follow-up when compared to matched controls over 12 months.

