Patients will be assessed for 12 months. After the baseline visit in which all the variables of the study will be collected, follow-up visits will be carried out every 6 months in both the control group and the intervention group. In these follow-up visits, researchers will assess the QoL of the PMCI/MD, adherence and compliance to prescribed medication, functional status, and service utilization. Researchers will also evaluate the QoL of caregivers and their burden. In addition, in the intervention group, TV-AssistDem user-behaviour data will be collected and usability will be evaluated.

Recruitment is scheduled to start in March 2019 and end in May 2019. Follow-up assessments will be ongoing and will be completed mid-2020.

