### Outcome measures

The primary outcome measure is the change in patient quality of life measured with the Quality of Life-Alzheimer’s Disease Scale (QoL-AD) [19–22]. Additional assessments will be used for secondary outcomes: caregiver quality of life and burden, patient treatment adherence and compliance, patient functional status and service utilization. TV-Assist Dem usability and other covariables will also be collected.

Patients will be assessed at baseline and at 6 months and 12 months after the beginning of the intervention. The assessments will be conducted under standardized conditions at the study centres.

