##### Service utilization

The Client Service Receipt Inventory (CSRI) [33, 34] scale will be used to evaluate the service utilization. This scale is an internationally used method for gathering data on service utilization and other domains relevant for economic analysis of mental health care. It has five sections: background client information, accommodation and living situation, employment history, earnings and benefits, a record of services usually used and information about informal caregiver support. The sections assessed will be consultations, admissions and visits in the last year, grouped into subsections according to hospital, specialist, primary or home care. Treatment related to hospital admissions or illness exacerbation will also be assessed. It’s adaptability ensures it is compatible with the research aims, context, participants’ likely circumstances, and the quantity and precision of information required. The CSRI will be administered via interview with PMCI/MD at baseline and at 12 months.

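### The economic analysis sets a 2-year horizon although the objective and data stop at 12 months, and its cost list omits the intervention cost that the hypothesis takes into account

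*Protocol article*

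**What the plan says.** **Horizon.** The Economic analysis section states: "The time horizon is 2 years and will include only direct health". Setting states: "Patients will be assessed for 12 months". Outcome measures gives the visit times: "Patients will be assessed at baseline and at 6 months and 12 months after the beginning of the intervention". The abstract names cost-effectiveness at 12 months as the secondary outcome, and the economic objective and hypothesis in Aims are both tied to 12 months of follow-up.

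**Costs.** The perspective is the payer's: "A cost-effectiveness and/or cost-utility analysis from a Health Service perspective (financer perspective) will be performed". The costs listed are "medication and healthcare use of services including outpatient and emergencies visits and hospital admissions". In Aims, lower healthcare costs are to be shown "after accounting for the estimated per patient costs of our intervention".

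**Service-use data.** Setting says of the 6-monthly visits: "In these follow-up visits, researchers will assess the QoL of the PMCI/MD, adherence and compliance to prescribed medication, functional status, and service utilization". Service utilization says: "The CSRI will be administered via interview with PMCI/MD at baseline and at 12 months". Table 1 agrees with Service utilization and has no entry for this inventory at 6 months.

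**The concern.** Two stated rules in one short section conflict with the hypothesis that the section is meant to test.

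First, a 2-year result needs either 2 years of data or a stated way of projecting the second year. The article describes neither, so the 2-year result would depend on an assumption that nobody has written down.

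Second, the platform's costs fall on one arm only. If they are left out, the comparison credits the intervention with any healthcare savings without charging for what produced them. A payer reading the result would then have the answer to a different question from the one in Aims.

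There is also a smaller wording conflict over whether service use is recorded at 6 months.

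**Working it through.** The plan gives no economic figure to reproduce apart from the horizon. The check therefore compares sections, with simple arithmetic.

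**1. Horizon against data**

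| Item | Time covered | Where stated |
|---|---|---|
| Economic horizon | 24 months | Economic analysis |
| Economic objective and hypothesis | 12 months | Aims; Abstract |
| EQ-5D-5L (utilities for QALYs) | 0, 6, 12 months | Caregiver quality of life; Tables 1 and 2 |
| Client Service Receipt Inventory (CSRI) | 0 and 12 months, each looking back one year | Service utilization; Table 1 |
| Calendar | Recruitment March to May 2019, follow-up complete mid-2020 | Setting |

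Unobserved time = 24 − 12 = 12 months, and 12/24 = 50% of the horizon. The calendar agrees: 24 months from March to May 2019 would run to March to May 2021, well past mid-2020. Counting from the start of the intervention rather than from randomisation moves this by the one to two weeks allowed for installation and changes nothing of substance.

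One possible origin of the 2 years is the pair of one-year CSRI look-backs, 12 + 12 = 24 months. That does not rescue the horizon. The first of those years precedes randomisation, so it holds no treatment effect, and no EQ-5D-5L was collected during it.

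**2. How much the unstated assumption matters (illustration)**

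Assume the utility gain rises linearly from 0 at baseline to *g* at month 12, with no discounting. The first-year QALY gain is ½ × *g* × 1 = 0.5*g*. The 2-year gain is then:

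- effect stops at month 12: 0.5*g* + 0 = 0.5*g*
- effect wanes linearly to zero by month 24: 0.5*g* + 0.5*g* = 1.0*g*
- effect persists: 0.5*g* + 1.0*g* = 1.5*g*

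With an assumed *g* of 0.05, these are 0.025, 0.05 and 0.075 QALYs. The same 12-month data support a threefold range.

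**3. Cost list against hypothesis**

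The article describes a set-top box, a webcam, a back-end server, an installation and training visit, support calls (six at most) and remote assistance by videoconference. None appears in the cost list of the Economic analysis section. Write *D* for the difference in listed healthcare costs (intervention minus control) and *C* for the part of the per-patient intervention cost that the health service bears. The hypothesis concerns *D* + *C*; the cost list taken literally gives *D*. The understatement is *C*.

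No value of *C* is given. For illustration only, assume a healthcare saving of 300 per patient (*D* = −300, any currency unit):

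| Assumed *C* | Cost list only (*D*) | With intervention cost (*D* + *C*) |
|---|---|---|
| 100 | −300 | −200 |
| 300 | −300 | 0 |
| 600 | −300 | +300 |

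The omission could change the sign of the result. The documents do not show that it would.

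**4. Service-use schedule**

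Setting implies recording at both 6-monthly visits; Service utilization and Table 1 give baseline and 12 months. The two specific sources agree with each other, and the one-year look-back at month 12 covers all of follow-up. What is left is a conflict of wording, with no gap in coverage.

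**The case against.** **A horizon beyond follow-up is legitimate, and an article need not describe the model.** Both statements are fair. But the article states its economic outcome, objective and hypothesis at 12 months, and the 2-year figure contradicts them. That mismatch stands even if a fuller document contains an extrapolation.

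**The restriction may only name a cost category.** It can be read as excluding non-health and indirect costs, as suits a payer perspective, with the listed services as examples and the intervention cost brought in through Aims. On that reading the sections are compatible and nothing is biased. This reading is possible, so the article does not demonstrate a bias. But the list is introduced as exclusive and names no platform item, so an analyst following that section alone would leave the cost out.

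**The size of any bias is unknown.** A reader might infer that the result is biased by exactly the full per-patient intervention cost. The documents do not support that: they give no cost and do not say who pays for the device, installation or support. Under a payer perspective only the payer's share counts.

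**The service-use schedule is not a design error.** A reader might go further and say that 20% × 240 = 48 patients would have no follow-up cost data, or that one-year recall by these patients is unsound. The 48 is an upper bound that assumes every expected loss misses the month-12 interview. A 6-month interview would recover only those lost after month 6, and that split is not given. The article contains no evidence on recall error. A shorter recall period or a caregiver co-informant is a design preference.

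**Conclusion.** The point holds in two parts. The 2-year horizon conflicts with an economic objective and data that end at 12 months, leaving 12 of 24 months (50%) unobserved with no extrapolation stated. The cost list omits the intervention cost that the hypothesis takes into account. If that list is followed literally, the incremental cost is understated in the intervention arm's favour by the health service's share of the intervention cost, an amount the documents do not give. The second part rests on taking the restriction in Economic analysis at its word; if Aims is meant to govern, the defect is one of drafting only.

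The disagreement between Setting and Table 1 on service use is a minor wording matter. All of this concerns one secondary outcome. It should be corrected, but it does not touch the QoL-AD analysis.

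**What to change.** In the Economic analysis section:

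1. Set the base-case horizon to 12 months from randomisation, matching the objective and the data. Present any 2-year result separately as a modelled extrapolation, stating how long costs and effects are assumed to last and the discounting used.
2. Add to the intervention arm the per-patient intervention costs that the health service bears: device, installation, training, calls and remote support. State who pays for each.

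In Setting, align the sentence on service utilization with Service utilization and Table 1 (baseline and 12 months). Adding the CSRI at 6 months is optional and is not needed to correct the error.

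The cost is a few sentences, a modest costing exercise for the platform, and possibly a less favourable cost result. No visit, questionnaire or sample-size change is required.

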#### User-behaviour analysis

Data on various platform usage variables will be collected for the intervention group. Regression analysis will be used to assess the relationship between the primary and secondary outcome variables and the usage variables in order to indicate which aspects of the platform use, most affect the outcomes. The results of the usability tests will be analysed using statistical methods to quantify the error rate, effectiveness and learning curve of the TV-AssistDem platform.

#### Missing data

Procedures can sometimes be considered when using statistical methods that fail in the presence of any missing values, or when in the case of multiple-predictor statistical models all the data for an individual would be omitted because of a missing value in one of the predictors. For analyses involving multiple regression analysis, a multiple imputation approach will be considered and used if statistically sound, depending on the proportion and pattern of missing values.

#### Methods to ensure validity and quality of data

Accurate and reliable data collection will be assured by verification and cross-check of the case report form (CRF) against the researcher’s records (source document verification). Source document verification will be conducted for 5% of data in subjects. A comprehensive validation check program utilizing front-end checks in the CRF will verify these data. Discrepancies and queries will be generated accordingly in the CRF for online resolution by the researcher at the site. In addition, the CRF data will be reviewed on an ongoing basis for medical and scientific plausibility.

#### Sample size

The main outcome measure is the total score of the QoL-AD, which ranges from 13 to 52. According to recent studies [40, 41], the standard deviation of the total score of the QoL-AD is 7.

For a minimum important clinical difference of 2.77 on the total QoL-AD score, with a standard deviation of 7, the effect size is 0.39. To compare two groups (Intervention and Control) using a two-sample, two-sided t-test with a 5% statistical significance level, the minimum number of evaluable patients required in each group is 100 (200 overall), to give a power of 80%. Given that it is a follow-up study, we must bear in mind that there will be losses along this one, therefore we will recalculate the sample size to take into account an expected percentage of losses of 20%. The number of subjects needed for each group will be 120 subjects (240 in total).

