### Limitations

Selection bias resulting from the missing data may be a potential limitation. Strategies such as the following will be carried out to diminish the latter: the sample size will be increased to 20% (expected losses), unreachable patients will be called three times in different days and hours and patients who do not attend the visits will be offered three additional appointments. A multiple imputation approach will be considered as dropout will be inevitable.

Researchers have received training on conducting the valid measures which will be used safely among older PMCI/MD and these assessments involve minimal risk. To ensure intervention standardization, it follows an exhaustive structured and professionals will be specifically trained. Furthermore, a manual for the researchers has been designed including: the working plan, the protocol, the different parts of the intervention and details to assess each variable. This will guarantee that the procedure can be replicated elsewhere.

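### The 20% loss allowance is added to the evaluable number, so 240 randomised leaves 192 evaluable, short of the protocol's own minimum of 200 (minor)

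*Protocol article*

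**What the plan says.** All the inputs are in the Sample size section of the protocol article. The target is stated as "For a minimum important clinical difference of 2.77 on the total QoL-AD score", and "with a standard deviation of 7, the effect size is 0.39". The test is specified as "using a two-sample, two-sided t-test with a 5% statistical significance level". On that basis "the minimum number of evaluable patients required in each group is 100 (200 overall"), "to give a power of 80" per cent.

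The section then turns to attrition: "we will recalculate the sample size to take into account an expected percentage of losses of 20" per cent. The result is "The number of subjects needed for each group will be 120 subjects (240 in total").

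The Limitations section returns to the allowance and lists it among the measures against bias from missing data: "the sample size will be increased to 20% (expected losses"). Taken literally, increasing something *to* 20% makes no sense. The evident meaning is an increase *by* 20%, which matches the step from 100 to 120.

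**The concern.** Three statements in the Sample size section cannot all hold: at least 100 evaluable per group, 20% expected losses, and 120 enrolled per group. A loss percentage applies to the patients who enter follow-up, so the enrolled number has to be the evaluable number divided by the retained fraction. Multiplying the evaluable number by one plus the loss fraction always falls short.

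The figure carries weight. The total of 240 is the recruitment target in the Abstract and under Participants, and Limitations presents the 20% increase as a safeguard against dropout, which it calls inevitable. A reader is led to think that 240 secures 80% power with 20% loss. On the protocol's own assumptions it does not quite do so.

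**Working it through.** **Inputs, all from the Sample size section:** difference 2.77 points; SD 7; two-sided alpha 0.05; two-sample t-test; power 80%; evaluable minimum 100 per group; losses 20%; enrolled 120 per group. Allocation is 1:1 (Randomization: blocks of four, two per group).

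**Step 1. Reproduce the evaluable number.**
Standardised difference d = 2.77/7 = 0.3957.
Normal approximation: n per group = 2 x (1.960 + 0.842)^2 / d^2 = 100.25.
The stated 100 is reproduced to within rounding.

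**Step 2. Reproduce the enrolled number.**
100 x (1 + 0.20) = 120 per group, 240 in total. This matches the protocol exactly, and it agrees with the description under Limitations.

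**Step 3. Apply the stated losses to the stated enrolment.**
120 x (1 - 0.20) = 96 per group, 192 in total. The stated minimum is 100 per group, 200 in total. The shortfall is 4 evaluable patients per group.

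**Step 4. Inflate for 20% loss.**
100/(1 - 0.20) = 125 per group, 250 in total, which is 10 more than stated. Check: 125 x 0.80 = 100.

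**Step 5. Losses that 120 per group can absorb.**
1 - 100/120 = 16.7%.

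**Step 6. Power of the stated test.** Noncentral t with 2n - 2 degrees of freedom and noncentrality d x sqrt(n/2):

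| Evaluable per group | Noncentrality | Power, t-test | Power, normal approximation |
|---|---|---|---|
| 100 | 0.3957 x sqrt(50) = 2.798 | 79.5% | 79.9% |
| 96 | 0.3957 x sqrt(48) = 2.742 | 77.9% | 78.3% |

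The allowance error costs 79.5 - 77.9 = 1.6 percentage points. The remaining half point to the nominal 80% is rounding in Step 1.

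**The case against.** Three arguments can be made for the protocol.

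*The 20% may be meant relative to the evaluable number.* Then 20 lost out of 120 leaves 100 and the figures agree. But that is a loss of 16.7% of those enrolled, and the text speaks of an expected percentage of losses in a follow-up study. Nothing in the article gives the phrase the other meaning.

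*The primary analysis is not a completers' t-test.* The Statistics section plans a linear mixed model, chosen because it can include patients with missing data, and QoL-AD is also measured at 6 months. A patient lost after that visit still contributes, so real power at 20% loss may exceed the t-test figure. This stands as a caution against treating 78% as the trial's actual power. It does not repair the calculation, which is expressed in evaluable patients under a t-test and makes its own loss correction. Nor can a reader conclude that the model, with or without baseline adjustment, wins back the lost power. That depends on correlations between visits and on the timing of dropout, and the article gives neither.

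*The effect is small.* This also stands, and it limits the point to a minor one.

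Two stronger criticisms are tempting. A reader might infer that the base figure of 100 is itself an error, since the exact t-test gives 101.2. That is a difference of formula and rounding, and power at 100 is 79.5%, which rounds to 80%. A reader might also rework everything from the printed effect size of 0.39 and find a larger gap. But 0.39 is 2.77/7 = 0.3957 cut to two digits. The design inputs are 2.77 and 7, and the stated 100 follows from those.

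**Conclusion.** Wrong as written, and minor. The 20% was added to the evaluable number instead of being taken off the enrolled number. With 240 randomised and 20% lost, 192 are evaluable against a stated minimum of 200. The enrolment consistent with the protocol's own figures would be 250. Power on the protocol's stated basis is about 78% instead of 80%.

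The inconsistency rests only on the article's numbers and on reading the loss percentage in its ordinary sense, as a share of those enrolled. The power figure further assumes a difference of 2.77, SD 7, equal losses in the two groups, and a t-test on evaluable patients.

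A reader might infer that the trial is materially underpowered or that recruitment has to be extended. The documents do not support that: the gap is 4 evaluable patients per group and about 1.6 power points.

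**What to change.** Keep 240 and correct the statement in Sample size in one of two ways:

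- *240 randomised; with 20% loss, 192 evaluable (96 per group), giving about 78% power for a 2.77-point difference with SD 7 (two-sided t-test, 5%)*; or
- *240 randomised, which retains 100 evaluable per group for losses of up to about 16.7%*.

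In either case, show the allowance as n/(1 - loss), and amend the sentence under Limitations so that it no longer presents the increase as full cover for 20% losses.

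Both versions cost wording only, and the stated power or the tolerated loss becomes slightly less favourable. If the sponsor prefers to keep both the 20% loss and the minimum of 100, the target becomes 250. That means ten more dyads and a change wherever 240 appears. A gap of this size does not require it.
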